### Interventions

#### Group A—acupuncture treatment

Participants in group A will receive 12 sessions of manual acupuncture treatment (3 sessions weekly for 4 weeks). The acupoints will include dubi (*ST35*), neixiyan (*EX-LE4*), ququan (*LR8*), xiyangguan (*GB33*), xuehai (*SP10*), sanyinjiao (*SP6*), taixi (*KI3*), and an ashi point (the point where the patient feels most pain) (Table 1 and Fig. 3). First, the adhesive pad will be applied on the skin of the acupoints according to WHO Standard Acupuncture Locations, and then single-use acupuncture needles (0.25 * 40 mm or 0.25 * 25 mm, Hwato, Suzhou, China) will be inserted into acupoints through the adhesive pad (Fig. 4). Acupuncturists will manually stimulate the needles to achieve de qi. The needles will be left for 30 min.

**Table 1 Tab1:** Locations of acupoints for acupuncture

Acupoints	Locations^a^
Dubi (ST 35)	On the anterior aspect of the knee, in the depression lateral to the patellar ligament
Neixiyan (EX-LE4)	On the anterior aspect of the knee, in the depression medial to the patellar ligament
Ququan (LR8)	On the medial aspect of the knee, in the depression medial to the tendons of the semitendinosus and the semimembranosus muscles, at the medial end of the popliteal crease
Xiyangguan (GB33)	On the lateral aspect of the knee, in the depression between the biceps femoris tendon and the iliotibial band, posterior and proximal to the lateral epicondyle of the femur
Xuehai (SP10)	On the anteromedial aspect of the thigh, on the bulge of the vastus medialis muscle, 2 cun superior to the medial end of the base of the patella
Sanyinjiao (SP6)	On the tibial aspect of the leg, posterior to the medial border of the tibia, 3 cun superior to the prominence of the medial malleolus
Taixi (KI3)	On the posteromedial aspect of the ankle, in the depression between the prominence of the medial malleolus and the calcaneal tendon

^a^1 cun (≈ 20 mm) is defined as the width of the interphalangeal joint of the participant’s thumb

**Fig. 3 Fig3:**
[figure not shown]
The location of acupoints. Red circles: location of non-acupoints. Blue circles: location of acupoints. Abbreviation: ST35, Dubi; EX-LE4, Neixiyan; LR8, Ququan; GB33, Xiyangguan; SP10, Xuehai; SP6, Sanyinjiao; KI3, Taixi; NA, non-acupoint

**Fig. 4 Fig4:**
[figure not shown]
The picture of acupuncture and sham acupuncture

#### Group B—sham acupuncture

Participants in group B will receive non-insertive acupuncture treatment on non-acupoints using the sham needles with blunt tip (0.25 × 40 mm or 0.25 × 25 mm, Hwato, Suzhou, China) (Fig. 4). Similar to the acupuncture group, the adhesive pad will be applied to the non-acupoints. Sham needles will not penetrate the skin and will not require the “De Qi” sensation. The needles will be left for 30 min. The acupuncture treatment will include 12 sessions for 4 weeks (3 sessions per week). The location of the non-acupoints is shown in Table 2 and Fig. 3.

**Table 2 Tab2:** Locations of non-acupoints for sham acupuncture

Acupoints	Locations^a^
NA1	On the anterior aspect of the thigh, 6 cun above the upper edge of the patella (between the spleen and stomach meridian)
NA2	On the anterior aspect of the thigh, 5 cun above the upper edge of the patella (between the spleen and stomach meridian)
NA3	On the anterior aspect of the thigh, 4 cun above the upper edge of the patella (between the spleen and stomach meridian)
NA4	In the middle of GB34 and ST36 (between the gallbladder and bladder meridian)
NA5	3 cun below GB34 (between the gallbladder and bladder meridian)
NA6	2 cun above the medial malleolus (between the liver and spleen meridian)
NA7	In the middle of GB40 and ST41 (between the gallbladder and bladder meridian)

*NA* non-acupoints

^a^1 cun (≈ 20 mm) is defined as the width of the interphalangeal joint of the participant’s thumb

#### Group C—waiting list

Participants in group C will not receive acupuncture within 4 weeks. After 4 weeks of observation, participants will receive 12 sessions of acupuncture treatment as free compensation.

During the treatment period, some other interventions, such as moxibustion, cupping, and massage, will not be allowed. Participants will withdraw from the study if they violate the protocol. When their pain is unbearable, they will be allowed to take non-steroidal anti-inflammatory drugs. Researchers should keep relevant records.

### Clinical outcome assessments

The primary outcome will be the response rate, which is defined as a decrease of more than 2 points on the NRS at week 4 compared with baseline [39]. NRS is a line divided into 10 segments. The degree of pain is assessed by 0–10 scores, and 0 score represents pain-free and 10 score represents the worst pain.

The secondary outcomes will be as following: (1) Pain subscale of Western Ontario and McMaster Osteoarthritis Index (WOMAC) scale will be used to evaluate the degree of knee pain of the participants. (2) Function subscale of the WOMAC scale will be used to evaluate the knee joint function. (3) Stiffness subscale of WOMAC will be used to evaluate the stiffness of knee joint. The severity of knee joint will increase with the higher scores of WOMAC. Participants will fill out the WOMAC scale at weeks 0, 2, and 4. (4) Blinding assessment and rescue medicine. (5) Stanford Expectations of Treatment Scale (SETS) will be used to assess participants’ positive and negative expectations of the upcoming treatment and their overall understanding of the purpose of the treatment. Participants will be asked to fill out the SETS scale before weekly treatment. (6) State-Trait Anxiety Scale-State Anxiety Subscale (STAI-S) will be used to evaluate the severity of current anxiety symptoms in participants with knee osteoarthritis. Participants will fill out the STAI-S scale at weeks 0, 2, and 4.

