## Abstract

**Background:**

Research on the effect of acupuncture has been limited. Whether the effect of acupuncture is equivalent to placebo has been the focus of debate in this field. This study will explore the specific and non-specific effects of acupuncture for knee osteoarthritis (KOA) by functional magnetic resonance imaging (fMRI).

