**Methods and design:**

Ninety participants diagnosed with KOA will be randomly divided into the acupuncture group, sham acupuncture group, and waiting list group in a ratio of 1:1:1. Except for the waiting list group, the other participants will receive acupuncture or sham acupuncture three sessions per week for 4 weeks respectively. The primary outcome will be the response rate which is defined on an individual basis as at least a 2-point decrease in the numerical rating scale (NRS) of pain at the end of intervention period compared with the baseline. fMRI scans will be performed at baseline and the end of the intervention period to examine the response of various brain regions. The secondary outcomes will include the Western Ontario and McMaster Osteoarthritis Index (WOMAC), State-Trait Anxiety Scale-State Anxiety Subscale (STAI-S), and Stanford Expectations of Treatment Scale (SETS). Pearson’s correlation coefficient will be performed to investigate the changes in brain activity and clinical variables.

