### Sample size

According to previous neuroimaging studies, in order to calculate statistical power for group-level fMRI studies, a sample size of 12 participants were required to achieve 80% power at the single voxel level when *α* = 0.05, and about 25 participants were required for a stricter threshold of *α* = 0.000002 [37, 38]. In this study, considering a 20% dropout rate and loss of data due to head motion, we plan to recruit 30 participants in each group. Each participant will receive 2 fMRI scans to explore different brain activity between the specific and nonspecific effects of acupuncture.

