### Statistical analysis

#### Clinical data analysis

The clinical data will be statistically analyzed by SPSS software (SPSS V.22.0 KO for Windows). Data will be described utilizing the mean (standard deviation) when following a normality assumption and using the median (quartile spacing) when the normality assumption is violated. The percentage (*n* %) will be used to describe the categorical variables. Comparisons between the three groups will be made by repeated-measures analysis of variance or Wilcoxon rank-sum (if normality is violated). For the primary outcome, we will calculate response rates at 4 weeks using the chi-square test. For the secondary outcomes, the mixed effect model and repeated measurement method will be used to compare the continuous variables (including WOMAC, SETS, and STAI-S).

The primary outcome will be performed using the intention-to-treat (ITT) and per-protocol (PP) analysis. ITT is defined as all randomized participants completing at least one post-baseline measurement. PP is defined as all the randomized participants who will not stop treatment prematurely, and complete 4 weeks of treatment, and undergo two MRI scans. The last observation carried forward (LOCF) will be used to estimate the missing values. The data will be considered statistically significant with a level of 0.05, and all hypothesis tests will be two-tailed.

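### The sample size rests on voxel-level fMRI power alone, while the primary outcome is a dichotomised NRS change tested without baseline adjustment; the detectable acupuncture-sham difference is about 33-36 percentage points

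*Protocol article*

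**What the plan says.** Under Clinical outcome assessments the article states: "The primary outcome will be the response rate". A responder is "defined as a decrease of more than 2 points on the NRS at week 4 compared with baseline"; the abstract (Methods and design) instead has "at least a 2-point decrease in the numerical rating scale (NRS) of pain". On the instrument: "The degree of pain is assessed by 0–10 scores".

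Under Clinical data analysis, for the primary outcome, "we will calculate response rates at 4 weeks using the chi-square test". No covariate or stratification is named. A mixed or repeated-measures model is to "compare the continuous variables (including WOMAC, SETS, and STAI-S"). NRS is not in that list, nor among the secondary outcomes. An earlier sentence in the same section plans a repeated-measures ANOVA or a rank-sum test for comparing the three groups without saying for which variables.

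The Sample size section cites neuroimaging work in which 12 participants were needed "to achieve 80% power at the single voxel level" with alpha 0.05, and about 25 at alpha 0.000002. It then plans 30 per group, allowing for 20% dropout and head-motion loss. The aims at the end of the Background define the specific effect as true versus sham acupuncture and the nonspecific effect as sham versus waiting list, and include estimating the proportion of each.

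**The concern.** The number that fixes the trial's size and the outcome declared primary belong to different questions. Voxel-level power says nothing about how well 30 per arm can separate two response proportions, and the article gives no other statement on that.

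Two analysis choices then add to the loss. Cutting an 11-level score into yes/no discards information in the primary test. Leaving baseline NRS out of that test ignores a variable that matters: entry requires NRS of 4 or more, and the room for a fixed absolute fall depends on the starting score.

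At stake are the acupuncture-sham comparison and the aim of apportioning specific and nonspecific effects. A share built from two differences in response rates inherits the imprecision of both.

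**Working it through.** **1. The plan's own figure.** Taking about 25 evaluable per group and 20% loss: 25 × 1.2 = 30, which reproduces the plan. Dividing instead, 25 / 0.8 = 31.25, gives 32. The 12 and the 25 cannot be re-derived, because no voxel effect size or SD is given. No clinical quantity enters at any step.

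**2. Power of the primary test.** Inputs from the article: 30 per arm, two-sided 0.05, uncorrected chi-square. Response rates are assumptions, since the article gives none. With p̄ the mean of the two rates and n per arm:

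- SE under the null = √(2p̄(1−p̄)/n); SE under the alternative = √((p₁(1−p₁)+p₂(1−p₂))/n)
- Power = Φ((|p₁−p₂| − 1.96 × SE null) / SE alternative)

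60% vs 40%: SE null = √(2 × 0.25/30) = 0.129; SE alternative = √(0.48/30) = 0.1265; power = Φ((0.20 − 0.253)/0.1265) = Φ(−0.42) = 34%. Exact enumeration gives 35%.

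60% vs 45%: SEs 0.129 and 0.1275; power = Φ((0.15 − 0.253)/0.1275) = Φ(−0.81) = 21%. Exact enumeration gives 22%.

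| Sham response (assumed) | Power, 15 points | Power, 20 points | Difference for 80% power |
|---|---|---|---|
| 30% | 22% | 35% | about 35 points |
| 40% | 22% | 35% | about 35 points |
| 50% | 22% | 35% | about 33 points |

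Powers are exact, at 30 per arm. Across exact and approximate methods the detectable difference is about 33-36 points. At 24 per arm (30 × 0.8) it is about 36-40 points. The 95% CI half-width at 60% vs 40% is 1.96 × 0.1265 = 0.248, about 25 points.

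**3. What continuous NRS with baseline would add.** Simulation, 30 per arm, scores rounded and truncated to 0-10, entry at 4 or more. All parameters are assumptions: baseline mean 6, SD 1.5; week-4 SD 2.2; correlation 0.5; mean sham fall 1.5.

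| True NRS difference | Chi-square, fall ≥ 2 | Chi-square, fall ≥ 3 | ANCOVA, week-4 NRS on arm and baseline |
|---|---|---|---|
| 1.0 | about 35% | about 35% | about 50% |
| 1.5 | about 61% | about 65% | about 83% |

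On integer scores, a fall of more than 2 means at least 3, so the two middle columns cover both wordings of the cut-off. The comparison comes out the same way under either.

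**4. Analytic cross-check.** Assume normal NRS change with equal variance at both times, and 40% vs 60% responders. The standardised difference is 0.253 + 0.253 = 0.507. The change score needs 2(1.96+0.842)²/0.507² ≈ 62 per arm. ANCOVA multiplies by (1+ρ)/2, which is 0.75 at ρ = 0.5, giving 46. The chi-square needs 97. With 30 per arm, ANCOVA power in this case is 57-68% for ρ from 0.7 down to 0.3: better than 34%, still below 80%.

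**The case against.** This is mainly an exploratory fMRI study, which explains the voxel-based sizing, and its Discussion concedes small groups. A responder endpoint with a cited cut-off and an unadjusted chi-square is valid in a randomised trial, and the outcome already uses change from baseline. Sensitivity analyses and covariates are often left to an analysis plan. That stands as far as validity goes: nothing here biases the test. It does not remove the mismatch, because the article itself fixes the primary outcome, its test and the sizing argument, and the conceded limitation is not tied to the primary outcome.

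Three stronger readings are tempting and not supported:

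- **Continuous NRS is analysed nowhere.** The repeated-measures sentence excludes no variable, and the mixed-model list is introduced as non-exhaustive. WOMAC pain is also kept as a continuous outcome. The information loss is certain only for the primary test.
- **A null acupuncture-sham result is likely whatever the truth.** That depends on the effect. At a 1.5-point NRS difference in the simulation, the chi-square has about 61% power, so significance is the more likely result.
- **The trial plans to read non-significance as equivalence.** The abstract says "Whether the effect of acupuncture is equivalent to placebo has been the focus of debate in this field"; that describes a debate, and no section plans such an inference.

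The 24-per-arm figures are also a pessimistic bound. Head motion does not remove an NRS score, and ITT with LOCF is planned, so the primary n should lie nearer 30.

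**Conclusion.** The point holds as a mismatch with an avoidable loss of precision, and the sponsor should act on it. The size was not derived from the primary outcome. If sham response lies between 30% and 50%, 30 per arm detects with 80% power only a difference of about 33-36 percentage points; power is about 22% at 15 points and 35% at 20. Adjusted continuous NRS gains roughly 15 to 22 percentage points of power in the two simulated cases. It does not by itself bring small effects to 80%, so it improves the analysis without curing the sizing. All power figures rest on assumed response rates and NRS parameters, because the article supplies none; the structural finding does not depend on them.

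**What to change.** 1. Keep the responder endpoint as primary, and support its test with logistic regression adjusted for baseline NRS.
2. Pre-specify as key secondary an ANCOVA of week-4 NRS on arm and baseline NRS, reporting acupuncture-sham and sham-waiting-list differences with 95% CIs. Use that scale to split specific from nonspecific effect.
3. In the Sample size section, state that the number was not derived from the primary outcome, and give the detectable difference at 30 per arm with the response rates assumed.
4. Reconcile the responder cut-off between the abstract and Clinical outcome assessments before any unblinded analysis.

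The cost is wording plus one or two extra models; the NRS scores are already collected. The downside is more than one NRS result to report and a less favourable precision statement.

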### MRI data acquisition

The MRI scan will be performed with a 3.0 Tesla superconductor (Skyra, Siemens, Erlangen, Germany) in the Beijing Hospital of Traditional Chinese Medicine Affiliated to Capital Medical University. Participants will undergo fMRI scans at baseline and the end of intervention. Before scanning, participants will be required to wear earplugs and headgear and remove all magnetic and metal items. The foam pad will be used to reduce head movement. Participants will be required to maintain a comfortable supine position and keep awake.

Scanning parameters: echo planar imaging (EPI) sequence will be used for resting fMRI scanning: repetition time (TR) = 2000 ms, echo time (TE) = 30 ms, field of view (FOV) = 224 mm × 224 mm, flip angle (FA) = 90°, layer thickness = 3.5 mm, axial slices = 32, size of voxel = 3.5 mm × 3.5 mm × 3.5 mm, in-plane resolution = 64 × 64, volumes = 240.

### Neurotransmitter and genetics assessment

Current neurophysiological studies showed that genetic variations in the neurotransmitter pathway mediating the placebo effect increased the possibility of identifying placebo responders through gene screening [40]. Given the subjectivity of clinical scales measurement, oxytocin, catechol-o-methyltransferase (COMT), and opioid receptor (OPRM1) will be tested to assess and predict the specific and nonspecific effects of acupuncture.

Participants will be fasted for at least 8 h before collecting the blood at the baseline, and venous blood will be drawn from the upper arm in the morning. Blood samples will be immediately centrifuged into two parts, plasma and blood cells, and will be stored in a refrigerator at − 80 °C. Finally, the samples will be processed in a technical laboratory by standard methods.

### Data management and monitoring

The case report form (CRF) will be used to record major clinical data, adverse events, and safety assessments during the study, with a unique numeric identifier for each participant. The clinical research assistant will validate the accuracy, missing, and consistent data in CRF. Clinical questionnaires will be administered to all participants in a separate room and administered by the same research. The clinical data will be independently entered into the EpiData electronic database by two researchers and tested by referring to the original data source when inconsistent data appears. EpiData electronic data will be exported to Microsoft Excel and then analyzed using SPSS software package (SPSS 12.0 ko for Windows). The participants will be scanned by a professional imaging doctor on the same machine, and after each scan, professional technicians will check the quality of the imaging data.

### Statistical analysis

#### Clinical data analysis

The clinical data will be statistically analyzed by SPSS software (SPSS V.22.0 KO for Windows). Data will be described utilizing the mean (standard deviation) when following a normality assumption and using the median (quartile spacing) when the normality assumption is violated. The percentage (*n* %) will be used to describe the categorical variables. Comparisons between the three groups will be made by repeated-measures analysis of variance or Wilcoxon rank-sum (if normality is violated). For the primary outcome, we will calculate response rates at 4 weeks using the chi-square test. For the secondary outcomes, the mixed effect model and repeated measurement method will be used to compare the continuous variables (including WOMAC, SETS, and STAI-S).

The primary outcome will be performed using the intention-to-treat (ITT) and per-protocol (PP) analysis. ITT is defined as all randomized participants completing at least one post-baseline measurement. PP is defined as all the randomized participants who will not stop treatment prematurely, and complete 4 weeks of treatment, and undergo two MRI scans. The last observation carried forward (LOCF) will be used to estimate the missing values. The data will be considered statistically significant with a level of 0.05, and all hypothesis tests will be two-tailed.

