### Informed consent and participant safety

Participants will be required to sign an informed consent (Additional file 2) and have the same chance to receive appropriate treatment. During the treatment, any adverse events, such as panic, subcutaneous hematoma, and pain, should be informed to the study researchers, who are responsible for monitoring and recording the adverse events and reactions throughout the study. If the participants cannot tolerate these adverse reactions, acupuncture treatment will be discontinued and the participants will be withdrawn from the study. There is no anticipated harm and compensation for study participation.

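### The set labelled ITT requires a post-baseline measurement, so no analysis of the primary outcome is defined on all 90 randomised participants

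*Protocol article*

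**What the plan says.** Under Clinical data analysis the protocol article states: "The primary outcome will be performed using the intention-to-treat (ITT) and per-protocol (PP) analysis". It then gives the definition: "ITT is defined as all randomized participants completing at least one post-baseline measurement". The per-protocol set needs full treatment over the 4 weeks and both MRI scans. No third set is named. The missing-data rule in the same section is "The last observation carried forward (LOCF) will be used to estimate the missing values".

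Two other sections decide who may have no data:

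- Informed consent and participant safety: for participants who cannot tolerate adverse reactions, "acupuncture treatment will be discontinued and the participants will be withdrawn from the study".
- The closing paragraph under Group C—waiting list, which reads as applying to all arms: "Participants will withdraw from the study if they violate the protocol".

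Neither section says whether outcomes are collected after withdrawal. On timing, Clinical outcome assessments defines response as "a decrease of more than 2 points on the NRS at week 4 compared with baseline". For other scales it says "Participants will fill out the WOMAC scale at weeks 0, 2, and 4" (STAI-S has the same weeks) and "Participants will be asked to fill out the SETS scale before weekly treatment".

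**The concern.** Intention-to-treat protects the comparison because everyone randomised is counted in the arm to which they were allocated. A set that requires a later measurement gives up part of that protection. People who leave early are removed from the denominator, and their reasons for leaving may relate both to arm and to outcome.

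Here that link is plausible. During the 4 weeks only the acupuncture and sham groups are needled, so stopping acupuncture for adverse reactions can arise only there. The waiting list is untreated and unblinded and may lose people for other reasons. The Background rests the study's two questions on true versus sham acupuncture and sham versus waiting list. Both contrasts would be estimated on groups selected after randomisation, under a label that tells readers otherwise.

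**Working it through.** **1. The plan's own figure.** Sample size gives about 25 per group for the stricter imaging threshold, a 20% allowance, and 30 recruited per group. 25 × 1.20 = 30 reproduces the figure. Dividing instead, 25 / (1 − 0.20) = 31.25, gives 32 when rounded up, which is close. The allowance is 30 × 0.20 = 6 per arm, for dropout and head-motion loss together.

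**2. Who is counted.** Setting the definitions side by side:

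| Participant | Set called ITT | Per-protocol |
|---|---|---|
| Completes treatment, both scans and week-4 NRS | in | in |
| Leaves after a qualifying measurement, no week-4 NRS | in, by LOCF | out |
| Leaves before any qualifying measurement | out | out |

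The third row appears in no analysis of the primary outcome. The text does not say which measurement qualifies. If any scale counts, the weekly SETS or the week-2 WOMAC and STAI-S would keep most later leavers in. If the NRS itself is required and is taken only at baseline and week 4, everyone without a week-4 NRS falls into the third row.

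**3. Illustration of size.** The response counts are assumptions; the documents give none. Take two arms of 30 with 15 and 9 responders, early leavers counted as non-responders, and an uncorrected Pearson chi-square:

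χ² = N(ad − bc)² / (product of the four margins).

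All randomised: 60 × (15×21 − 15×9)² / (30×30×24×36) = 60 × 180² / 777,600 = 2.50, so p = 0.114.

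Now delete k non-responders from the first arm only:

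| k deleted | First arm | Shift in rate | p against 9/30 |
|---|---|---|---|
| 0 | 15/30 = 50.0% | 0 | 0.114 |
| 3 | 15/27 = 55.6% | +5.6 points | 0.051 |
| 4 | 15/26 = 57.7% | +7.7 points | 0.037 |
| 6 | 15/24 = 62.5% | +12.5 points | 0.017 |

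**4. Type I error on the same assumptions.** With equal true response rates, k non-responders deleted from one arm, and exact binomial enumeration at nominal two-sided 0.05:

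| True rate (assumed) | k = 0 | k = 3 | k = 6 |
|---|---|---|---|
| 0.4 | 0.049 | 0.074 | 0.129 |
| 0.5 | 0.052 | 0.088 | 0.175 |

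Both tables assume that every deleted person is a non-responder and that all deletions fall in one arm. Deletions from the other arm, or spread over both, would move the comparison differently.

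**The case against.** The set is openly defined, a per-protocol analysis accompanies it, and only very early leavers are excluded. With weekly and week-2 questionnaires these may be few. That is fair, and it limits the likely size of the problem. It does not make the set intention-to-treat.

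Four stronger readings are tempting, and the documents do not support them:

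- *A reader might apply the full 20% loss to the ITT set and infer shifts of 10 to 20 points.* The 20% also covers head-motion loss, which leaves the NRS intact, and dropouts after a qualifying measurement stay in. Six per arm is at most an upper bound within that allowance, and any responder count is an assumption.
- *A reader might infer that the week-4 NRS is never collected after withdrawal.* The article says that people are withdrawn from the study and is silent on later outcome collection. The full protocol, which Data Availability mentions, may address it.
- *A reader might infer that the waiting list will seek prohibited therapy more often.* Nothing says so. The free acupuncture after week 4 and the permitted anti-inflammatory drugs could help retention. Unequal loss is possible, but its direction is unknown.
- *A reader might infer that LOCF treats similar withdrawals inconsistently.* This depends on whether the NRS is taken between baseline and week 4, and the schedule figure is not available here. If it is not, LOCF carries the baseline value forward, the change is zero, and a retained person with no week-4 value is already a non-responder.

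**Conclusion.** The point holds. The definition is explicit and mislabelled: it is a modified ITT set conditioned on a post-randomisation event, and no analysis of the primary outcome is defined on all 90 randomised. The withdrawal rules can produce excluded participants, though they need not, because only withdrawal before the first qualifying measurement has that effect.

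The size of any bias cannot be derived from the documents and may be small. The calculations show only that, with 30 per arm, a few one-sided exclusions matter: under the assumed 15/30 versus 9/30, four deletions are enough to cross 0.05. That result rests on assumed response rates, on all exclusions being non-responders, and on their falling in one arm.

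**What to change.** - Define ITT as all randomised participants, analysed in the arm to which they were allocated. If the present set is kept, call it modified ITT and say which measurement qualifies.
- Reconcile Clinical data analysis with the two withdrawal rules, so that the week-4 NRS is sought from everyone who stops treatment or violates the protocol unless consent is withdrawn. The rules for stopping treatment stay as they are.
- For the primary responder endpoint, count a still-missing week-4 NRS as non-response in all arms. Add a sensitivity analysis such as multiple imputation, since counting missing as failure is itself an assumption and weighs against whichever arm loses more people. If the NRS is taken only at baseline and week 4, this agrees with LOCF for those already retained and changes the result only for those now excluded.

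The cost is a change of wording, one week-4 contact for those who stopped, and possibly slightly lower response rates. The change is best made while recruitment continues, because a week-4 NRS that was not collected cannot be recovered later.

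### The set labelled ITT leaves out randomised participants with no post-baseline measurement, so neither planned analysis of the primary outcome covers all 90 randomised

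*Protocol article*

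**What the plan says.** Under Clinical data analysis, the protocol article states: "The primary outcome will be performed using the intention-to-treat (ITT) and per-protocol (PP) analysis". It then fixes the two sets. For the first, "ITT is defined as all randomized participants completing at least one post-baseline measurement". The per-protocol set takes those who do not stop early, "complete 4 weeks of treatment, and undergo two MRI scans". For gaps in the data, "The last observation carried forward (LOCF) will be used to estimate the missing values".

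Under Clinical outcome assessments, response is "a decrease of more than 2 points on the NRS at week 4 compared with baseline". The text gives no other post-baseline time for the pain rating. Other instruments are collected earlier: "Participants will fill out the WOMAC scale at weeks 0, 2, and 4", the anxiety scale has the same times, and for expectations "Participants will be asked to fill out the SETS scale before weekly treatment".

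The Sample size section plans 30 per group, "considering a 20% dropout rate and loss of data due to head motion".

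**The concern.** Intention-to-treat means everyone randomised, analysed in the allocated arm. A set that requires post-baseline data is selected by events after randomisation, so it no longer has the full protection of randomisation, although readers will assume from the label that it does.

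Unequal loss between arms is foreseeable here. The waiting list cannot be blinded (Blinding). Participants who cannot tolerate adverse reactions to needling are withdrawn (Informed consent and participant safety), which cannot happen on the waiting list during the four weeks. Participants who use disallowed treatments also leave the study (Group C—waiting list), and the temptation may differ by arm. The trial rests on two contrasts, acupuncture against sham (A−B, specific) and sham against waiting list (B−C, nonspecific), and aims to state the proportion of each. A proportion formed from differences in response rates is sensitive to the denominators.

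Because the qualifying measurement is not named, the same event, a missing week-4 pain score, can be handled in different ways.

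**Working it through.** **Inputs from the article:** 90 randomised, 30 per arm; a 20% allowance covering dropout and head-motion loss together; two-sided 0.05; chi-square test on the response rate. The article gives no response rates and no losses by arm, so all such values below are assumptions.

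**The plan's own figure.** The Sample size section starts from about 25 per group. 25 × 1.20 = 30, the stated number. Dividing instead gives 25 / 0.80 = 31.25, rounded up to 32, which is close. A 20% loss from 30 is 6 per arm, or 18 in total.

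**Step 1: who is in the set.**
- If the qualifying measurement is the pain rating, taken only at baseline and week 4 as the text reads, the set is exactly those with a week-4 rating. Carrying forward then has nothing to fill for the primary outcome.
- If any measurement counts, someone who leaves after the week-2 questionnaires stays in. The only earlier pain rating is the baseline one; carrying it forward gives a change of zero, hence non-response. Someone who leaves before any post-baseline measurement is removed.

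**Step 2: size of the set.** Take the whole 20% as people without a week-4 rating. This is an upper bound, because head-motion loss need not remove a pain score.

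| Share of the lost with a qualifying measurement | Set per arm | Total | Response rate if 12 of the 24 observed respond |
|---|---|---|---|
| none | 24 | 72 | 12/24 = 50.0% |
| half | 27 | 81 | 12/27 = 44.4% |
| all | 30 | 90 | 12/30 = 40.0% |

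**Step 3: effect on the contrasts.** Assume 13, 10 and 3 responders of 30 in A, B and C, all losses among non-responders, and none of the lost qualifying. Specific share = (A−B)/(A−C).

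| Excluded (A/B/C) | A | B | C | A−B | Share |
|---|---|---|---|---|---|
| 0/0/0 | 13/30 = 43.3% | 10/30 = 33.3% | 3/30 = 10.0% | 10.0 points | 30% |
| 6/6/6 | 13/24 = 54.2% | 10/24 = 41.7% | 3/24 = 12.5% | 12.5 points | 30% |
| 3/9/6 | 13/27 = 48.1% | 10/21 = 47.6% | 12.5% | 0.5 points | 1.5% |
| 9/3/6 | 13/21 = 61.9% | 10/27 = 37.0% | 12.5% | 24.9 points | 50% |

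Equal loss inflates the difference by 1/0.8 but leaves the share at 30%. The large swings need a threefold imbalance in loss.

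**Step 4: type I error.** Two arms of 30, Pearson chi-square without continuity correction at 0.05, by simulation.

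| Assumed loss and null | Lost excluded | Lost counted as non-response |
|---|---|---|
| 10% vs 30%; 40% success in both arms, loss counted as failure | 14.5% | 4.9% |
| 15% vs 25%; same null | 7.5% | about 5% |
| 10% vs 30%; loss unrelated to outcome, 40% response in both arms | about 5% | 9.8% |

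In the third row, counting loss as non-response turns equal response into 0.40 × 0.90 = 36% against 0.40 × 0.70 = 28%, which explains its inflated error.

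**The case against.** The strongest reply is that sets of this kind are common, that the fault is one of label, and that the size of any bias is unknown. Much of this stands. The number with no post-baseline data is not given, part of the 20% is imaging loss, and the large distortions in step 3 come from assumed losses that are very unequal and confined to non-responders. Counting every missing score as non-response is not neutral either, as the last row of step 4 shows. For anyone already admitted under the broad reading, carrying the baseline forward gives non-response anyway, so the real change concerns those with no post-baseline data at all.

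A reader might infer two stronger things. One is that the primary analysis is in effect a completer analysis. That requires the week-4 pain rating to be the only qualifying measurement. The article does not say so; it asks for at least one measurement, provides for carrying values forward, has week-2 questionnaires, and defines a separate per-protocol set that is the real completer set.

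The other is that entry to the set runs on a different clock in the waiting list, because expectations are recorded before weekly treatment and that group has none. This requires the expectation scale to qualify and not to be collected weekly in the waiting list. Neither is stated; the pain, knee and anxiety measures have the same weeks in all arms, and the schedule figure is not shown. The two inferences also need opposite readings of the rule, so they cannot both hold.

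The objection does not remove the stated rule: the set called ITT is not everyone randomised, and the other set is smaller.

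**Conclusion.** The point holds as a fault in a stated definition. The label is wrong, no planned primary analysis covers all 90, and the rule leaves open who is admitted. At the upper bound of 20% missing pain scores the set could be anywhere from 72 to 90 people.

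Bias in the A−B and B−C contrasts is possible because loss by arm is foreseeable, but its size and direction cannot be read from the article. Under the assumed 10% against 30% loss, exclusion does harm if leaving amounts to failure and little harm if leaving is unrelated to outcome. In the second case the simple count-as-failure rule is the worse of the two. That is a reason to analyse everyone under one declared rule and to test it, not a reason to keep the present set as the main one. The point is one that should be fixed, short of a fatal flaw.

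**What to change.** In Clinical data analysis:

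1. Define the ITT set for the primary outcome as all 90 randomised participants in their allocated arms, with no post-baseline requirement.
2. State one rule for a missing week-4 pain rating and apply it alike in all three arms, for example non-response.
3. Add a sensitivity analysis by multiple imputation within arm, using baseline pain rating and the WOMAC pain scores already collected at weeks 0 and 2. Step 4 shows why it is needed: no single rule is safe under every pattern of loss.
4. Relabel the present set modified ITT, name the measurement that admits a participant, and keep it as supportive.

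The cost is a change of wording and one extra analysis, with no additional participants or visits. Stated response rates will be slightly lower under a non-response rule. The change should be made before the allocation is revealed to the analysts.
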